## Methods/Design

### Trial design

This is a prospective, randomized, controlled trial, involving four assessment time points (baseline, post-intervention, one-year follow-up and five-year follow-up) and three groups (experimental treatment, standard treatment and control without treatment). Participants are a self-selected group that will be assigned randomly to either the experimental, standard or control group. The longitudinal design will allow the evaluation of the short- and long-term effects of the intervention. Figure 1 shows the overall design of this project. All study procedures, written information and consent forms received approval from the local ethics committee (Landesärztekammer Rheinland-Pfalz, file number: 837.380.13/9065-F) and the University Medical Center data protection official. To report this randomized controlled trial we made use of the CONSORT guidelines [52,53].

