### Randomization

Following baseline assessment, the participants are allocated to one of the three conditions: MediMind, Autogenic Training or control group. Participants with informed consent are stratified randomized initially by course of study (medical versus dental), semester (2nd or 8th) and gender. This was due to control for potential confounding effects and secure homogenous distribution among groups. The randomization to the groups will be with an allocation ratio 2 (MediMind) : 2 (Autogenic Training) : 1 (control group), for ensuring a maximum power for analysis between MediMind and Autogenic Training. After stratification the groups are randomized by drawing lots using the aforementioned allocation ratio. The randomization to the groups will be done by an independent member of institute not involved in this project, ensuring that trainers and recruiters are kept blind to the allocation of each participant. Treatment participants are openly informed into which group they are allocated. Additionally, participants in the control group will be informed of their status and the opportunity to attend MediMind when data collection is completed after five years. Over these five years participants of the control group get no intervention but are invited to fill out the questionnaires at each of the four assessment time points.

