### Outcome measures

#### Assessment time points

Measures will be completed by all participants at four assessment time points: (1) baseline, after receiving signed informed consent and before random assignment to the study groups; (2) post-intervention, three weeks after the last training session; (3) follow-up, one year after post-intervention assessment; (4) follow-up, five years after post-intervention assessment. At each assessment time point, participants complete the same questionnaires and standard demographic measures, which take approximately 45 minutes. Additionally, starting with post-intervention, questions relating to stressful life events will be added. The participants will be able to complete the baseline questionnaires after the information lectures or complete an online version. In order to participate in the post-intervention and follow-up assessments, the participants will have the choice of either filling in the questionnaire as a paper-and-pencil version or completing an online version. As an acknowledgment of their participation, 50.- € vouchers will be raffled among the participants. As a special motivation to the participants that have been allocated to the control group, everyone who participated in the questionnaire surveys will receive a 20.- € voucher.

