### Statistical methods

Descriptive statistics on study population will be calculated for each group at baseline. Means and standard deviations on primary, co-primary, secondary outcome and additional measures will be presented at baseline, post intervention and at the two follow-up time points for each group. A two-folded approach according to Tabachnik and Fidell [75] is used to address missing data. Initially, a Completer-Analysis with a sample of complete data-sets of each person is evaluated. Secondly, an Intent-to-Treat-Analysis with a Last-Observation-Carried-Forward-Method will be applied to check for differences and possible drop-out-effects. The null hypothesis will be rejected at the cut-off of 5% (α-level), therefore a *P* value ≤ .05 will be applied. To evaluate all group x time interactions in one model, we will use an explicatory MANOVA with primary, co-primary and secondary outcome. We expect differential time x group effects on secondary outcome at the one year/five year follow-up after post-intervention assessment. Therefore, this preliminary analysis will be called ‘explicatory’. For confirmatory analysis following the assumption that primary and co-primary outcome are separate hypothesis, both hypotheses will be tested in separate repeated-measures ANOVA’s with the factorial structure group (MediMind, Autogenic Training and control group) x time. The hypothesis will be evaluated through testing interaction effects. Orthogonally constructed comparisons are then used to check for pairwise differences. If needed, Holm-Bonferroni corrected pairwise comparisons will be used [76]. Additionally post-hoc sub-group comparisons (sex, semester, cohort) will be conducted to analyze data sets furthermore.

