## Discussion

Our study is the first to evaluate the effectiveness of a mindfulness-based intervention for medical students in Germany in a randomized controlled setting with both treatment groups, MediMind and Autogenic Training, and a control group without treatment. With the possibility of controlling several confounding aspects, the analysis will be based on an experimental design with good power.

One possible limitation of the study might be a motivational bias of the selected participants. It can be assumed that mainly highly motivated students volunteer to take part in a weekly training with an additional time requirement beside the high workload of their curriculum. Possibilities to generalize the results may be limited to students of high motivation and interest in the concept of mindfulness and Autogenic Training. Furthermore, the response rate at the time of post-intervention might be affected as the data cannot be collected directly at the end of the last training session. The students will be asked to send back a paper-and-pencil version of the questionnaire or to complete an online version. Considering the fact that participants of the control group do not benefit from the training until the data collection is completed after five years, the motivation of this specific study group to complete the questionnaires at post-evaluation is expected to be challenging. Further drop-outs could occur one year or five years post-intervention, as participants will be harder to reach or no longer motivated. In order to minimize a reduction in sample size, monetary vouchers will be raffled among the participants. Another limiting effect might be the inclusion of students at different stages of their studies. The experience of stress might differ between the second and eighth semester, and therefore, the effect size of a pre-post effect of the intervention is supposed to be smaller in the advanced semester.

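### The confirmatory group × time ANOVA is valid but uses baseline only as a level of time; baseline as a covariate would give more precise treatment comparisons from data already collected

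*Protocol article*

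**What the plan says.** **Design.** The trial is described as "involving four assessment time points (baseline, post-intervention, one-year follow-up and five-year follow-up". The first assessment is taken at "baseline, after receiving signed informed consent and before random assignment to the study groups" (Assessment time points), with the same questionnaires at every wave. Participants are "stratified randomized initially by course of study (medical versus dental), semester (2nd or 8th) and gender" (Randomization). The reason given is: "This was due to control for potential confounding effects and secure homogenous distribution among groups". Allocation is "allocation ratio 2 (MediMind) : 2 (Autogenic Training) : 1 (control group").

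**Analysis.** For the primary outcome (TICS) and the co-primary outcome (Brief COPE), "both hypotheses will be tested in separate repeated-measures" ANOVAs (Statistical methods). The factors are group and time, and each hypothesis is judged on the interaction. No baseline covariate and no stratification factor is named. Sex and semester, together with cohort, return only in post-hoc subgroup comparisons; course of study is not named there. The ANOVA sentence does not list the levels of time. Taking baseline as the first level follows from the four-wave design.

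**The concern.** The confirmatory model is positively stated, so this is a choice and not a detail left for a later document. When baseline is a level of time, the treatment comparison between baseline and any later wave is a comparison of change scores. A change score subtracts the whole baseline value. Regression on baseline subtracts only the part that predicts follow-up, so its variance is smaller for any correlation below 1.

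Precision is scarce here. The control group receives one fifth of participants, up to half of the sample may be lost by five years, and the Discussion expects completion in the control group to be difficult. A second question is whether leaving the stratification factors out of the model adds to the loss.

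**Working it through.** **1. The plan's own figures.** 420 × 0.30 = 126 recruits per term, and 126 × 3 × 0.50 = 189 at five years. Both reproduce. The 126 given as the minimum at five years comes from G*Power and cannot be recomputed, because no effect size, power or within-person correlation is stated. At 2:2:1, 126 splits into 50.4 : 50.4 : 25.2, taken as 50 : 50 : 25.

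**2. Variance of a baseline-to-follow-up contrast.** Assume equal SD at both waves and correlation r.
- Change score: 2(1−r) SD².
- Baseline as covariate: (1−r²) SD².
- Ratio: (1−r²) / [2(1−r)] = (1+r)/2.

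**3. Power.** Two-sided 5% test, noncentral t, assumed effect d = 0.5 SD, noncentrality d / √[v(1/n₁ + 1/n₂)], where v is the variance from step 2. For example, at r = 0.5 with 50 against 50: 0.5/√(1.00 × 0.04) = 2.50 for change, and 0.5/√(0.75 × 0.04) = 2.89 adjusted.

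| Assumed r | Ratio | Participants matching 126 | Power, 50 v 50 | Power, 50 v 25 |
|---|---|---|---|---|
| 0.3 | 0.65 | 82 | 55% → 74% | 40% → 56% |
| 0.5 | 0.75 | 95 | 70% → 82% | 52% → 64% |
| 0.7 | 0.85 | 108 | 89% → 93% | 74% → 81% |
| 0.8 | 0.90 | 114 | 97.5% → 98.5% | 89% → 92% |

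The third column is 126 × ratio, rounded up. With the expected 189 (75 v 75) and r = 0.5, the same formula gives 86% → 94%.

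**4. More than one follow-up wave.** For the mean of three post-baseline waves against baseline, with all correlations equal to r, the two variances are:
- change: (1+2r)/3 + 1 − 2r;
- adjusted: (1+2r)/3 − r².

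The ratio is 0.48, 0.63 and 0.78 at r = 0.3, 0.5 and 0.7, so the gain does not depend on using a single follow-up wave.

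**5. Stratification factors.** A simulation used 3,000 runs per setting, two waves, arms of 52/50/24 and six assumed strata. The assumed effects were 0.5 SD for MediMind and 0.25 SD for Autogenic Training against control. Power of the three-group test:

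| Stratum effect (assumed) | r | Group × time | + strata | Baseline covariate | Baseline + strata |
|---|---|---|---|---|---|
| 0.4 SD, constant over time | 0.5 | 43.8% | 43.9% | 56.5% | 56.0% |
| 0.4 SD, constant over time | 0.7 | 64.7% | 64.6% | 72.8% | 72.4% |
| plus 0.4 SD change over time | 0.5 | 40.8% | 43.7% | 44.9% | 55.5% |
| plus 0.4 SD change over time | 0.7 | 61.0% | 66.5% | 62.0% | 73.4% |

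A constant stratum effect cancels within persons, so omitting it costs nothing. If strata alter the time course, adding them to the group × time test gains 2.9 and 5.5 points. Without them, that test's type I error was 3.2% and 2.9%, which is conservative. In the same settings most of the gain from the baseline covariate appears only once the strata are also in the model.

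**The case against.** **Nothing is invalid.** A group × time ANOVA judged on the interaction is a sound test in a randomised trial, and it does use baseline. A reader might infer that baseline is ignored, or that omitting the strata makes the test anti-conservative. Neither holds: baseline is a level of time, and the omission leaves the test valid or slightly conservative. Stratified allocation secures similar groups whatever model is fitted. This objection stands and limits the point to efficiency.

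**The strata matter only conditionally.** A reader might also infer that the plan itself expects different time courses by semester, since "The experience of stress might differ between the second and eighth semester" (Discussion). That sentence describes a level of stress, and a level difference cancels. It goes on to predict a smaller pre-post effect of the intervention in the later semester. That is modification of the treatment effect, which the planned semester comparison addresses directly. It does not directly state a stratum-specific time course.

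**The size is assumed.** No correlation, SD, effect size or power is stated. TICS looks back three months, and the post-intervention assessment falls three weeks after a five-week course, so its recall period reaches back before training began. This argues against a low r at that wave, where the gain would then be smaller. At one and five years r may be lower and the gain larger. The 126 is a five-year minimum for the secondary outcome, whereas this point concerns the primary and co-primary outcomes, for which more participants may be available. These are fair limits on the figures, but the adjusted variance is still smaller at every r below 1.

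**The effect measure was chosen for the interaction model.** Partial eta-square was picked to quantify the interaction, so a change of model means redefining it. This is a real cost.

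**Conclusion.** The confirmatory analysis is valid, but it gives up precision that the design has already paid for. For a baseline-to-follow-up contrast, adjusting for baseline reduces the variance by 35%, 25%, 15% and 10% at r = 0.3, 0.5, 0.7 and 0.8. That is worth about 19, 12, 4 and 1 points of power at 50 v 50 and d = 0.5. Against the smaller control arm (50 v 25) the gain is about 16, 12, 7 and 3 points.

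The direction follows from algebra, given equal SDs. The size cannot be fixed from the document: r, d, the arm sizes and the two-wave simplification are assumptions, and the omnibus test over four waves will give other figures. The stratification part is secondary. It costs nothing if stratum effects are constant over time and about 3 to 6 points under an assumed 0.4 SD stratum-by-time effect.

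**What to change.** For the confirmatory analysis of TICS and Brief COPE, take the post-intervention, one-year and five-year scores as outcomes. Include group by time, baseline score by time, and course, semester and gender as fixed effects, with time interactions where numbers allow. Test the group effect at the post-baseline waves, and state which waves enter the test.

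The test should not be reduced to group × time among the post-baseline waves alone. That would ask only whether the effect changes after the intervention. The joint test of group at three waves has 2 × 3 = 6 degrees of freedom, the same as the planned interaction, (3−1) × (4−1) = 6. Because randomisation makes the groups equal at baseline in expectation, it addresses the same null hypothesis.

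**Cost.** With every covariate crossed with time, 4 terms × 3 waves = 12 extra parameters, fewer if some time interactions are dropped. The hypothesis and the partial eta-square must be restated as baseline-adjusted group effects. No new data are needed.

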### Primary and secondary aim

The primary aim of this research is to examine the effectiveness of a mindfulness-based stress prevention training for medical students (MediMind). It is hypothesized that MediMind will be more effective in the reduction of stress and prevention of psychological morbidity as a standard treatment and more effective than a control condition. The evaluation will be based on an interaction-related stress concept [50], in which stress is defined as a nonmatch between requirements and the resources available to a person according to the transactional model of stress and coping by Lazarus [51]. Therefore, we expect MediMind to have a beneficial effect on the experience of stress and coping strategies as primary and co-primary outcome. Furthermore, as secondary outcome we expect MediMind to have a preventive effect on psychological morbidity that will be visible only after reviewing the follow-up surveys.

The secondary aim of this research is to examine the effect of MediMind on risk factors associated with psychological morbidity in medical students compared to a standard treatment and a control condition. It is expected that MediMind has a beneficial effect on rumination as a coping style in response to dysphoric mood and personality traits like impulsivity, perfectionism, self efficacy expectations, locus of control and self-esteem. In this context we expect MediMind to have a positive effect on satisfaction with life of the participating medical students. Additionally, a measure of mindfulness will be included to assess the expected improvement in mindfulness by participation in MediMind.

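### The confirmatory rule does not match the hypotheses: the interaction test is undirected, the orthogonal comparisons can cover only one of the two hypothesised pairs, and the step that covers both is optional

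*Protocol article*

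**What the plan says.** The section Primary and secondary aim states a two-part, directed hypothesis. MediMind is to be superior in stress reduction and in "prevention of psychological morbidity as a standard treatment and more effective than a control condition". I read this as two claims: better than Autogenic Training, and better than no treatment.

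The section Randomization shows which comparison matters most. The ratio is "allocation ratio 2 (MediMind) : 2 (Autogenic Training) : 1 (control group), for ensuring a maximum power for analysis between MediMind and Autogenic Training".

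The section Statistical methods fixes the confirmatory analysis in four steps:
- For the primary and co-primary outcomes, "both hypotheses will be tested in separate repeated-measures ANOVA’s with the factorial structure group (MediMind, Autogenic Training and control group) x time".
- The criterion: "The hypothesis will be evaluated through testing interaction effects".
- The follow-up: "Orthogonally constructed comparisons are then used to check for pairwise differences".
- A conditional step: "If needed, Holm-Bonferroni corrected pairwise comparisons will be used".

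The article does not say when the last step is needed. It also does not say which pairwise results are required before MediMind is called superior. The section Effect size reports partial eta-square, which has no direction either.

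**The concern.** The hypotheses are two signed differences between named arms. The stated criterion asks only whether any group's course over time differs from any other's. It can be met when the two trainings are equally good, or when Autogenic Training works and MediMind does not.

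The follow-up that should resolve this is described as a set of orthogonal comparisons. Two pairwise differences that share an arm are not orthogonal, so the named tool does not fit the task. The one tool that does fit is left to discretion. At stake is whether the report's main statement, that MediMind is better than standard training and better than nothing, rests on the tests that address it.

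**Working it through.** **Inputs from the article.** Three groups, four time points, allocation 2:2:1, 5% level. At least 126 participants are wanted at five years, and 189 are expected. The recruitment arithmetic reproduces: 0.30 × 420 = 126 per semester, and 3 × 126 × 0.5 = 189. The required minimum of 126 cannot be recomputed, because no effect size, SD, correlation or power is given.

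**Inputs assumed.** SD 1; correlation 0.5 between any two waves; an effect of 0.5 SD that is constant after baseline (range 0.3 to 0.8 shown); 50/51/25 completers for 126 and 76/75/38 for 189.

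**1. Direction and degrees of freedom.** The interaction has (3 − 1)(4 − 1) = 6 degrees of freedom. It is an F test, so it carries no sign.

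**2. Orthogonality (no assumption needed).** Write the contrasts over (MediMind, Autogenic, control).
- MediMind minus Autogenic is (1, −1, 0) and MediMind minus control is (1, 0, −1). The product of coefficients is 1·1 + (−1)·0 + 0·(−1) = 1, not 0.
- With group shares 0.4, 0.4 and 0.2, and up to a common factor, the covariance is 1/0.4 = 2.5. The variances are 1/0.4 + 1/0.4 = 5 and 1/0.4 + 1/0.2 = 7.5. The correlation is 2.5/√(5 × 7.5) = 2.5/6.12 = 0.41.
- The covariance equals one over the size of the MediMind arm, so no allocation ratio makes it zero.
- Three groups allow two mutually orthogonal contrasts. The partner of (1, −1, 0) is (½, ½, −1), both trainings averaged against control, which the article does not hypothesise.

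**3. How often the interaction is significant when MediMind is not better than Autogenic Training** (simulated 3 × 4 repeated-measures F test, 4,000 runs per scenario):

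| True state | 126 completers | 189 completers |
|---|---|---|
| Both trainings 0.3 SD better than control | 18% | 27% |
| Both trainings 0.5 SD better than control | 50% | 71% |
| Both trainings 0.8 SD better than control | 92% | 99% |
| Only Autogenic Training works, 0.5 SD | 71% | 89% |

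A closed-form check of the second row at 126, taking a 2-df test on a change score with SD 1: the group means are 0.5, 0.5 and 0, and the weighted mean is 0.8 × 0.5 = 0.4. The noncentrality is 126 × (0.8 × 0.1² + 0.2 × 0.4²) = 126 × 0.04 = 5.04, which gives 50% power.

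**4. What happens if pairwise tests follow.** I repeated the simulation with 10,000 runs per scenario and 126 completers. The pairwise tests used mean post-baseline change at an uncorrected 5%, only after a significant interaction.
- Both work equally: MediMind–Autogenic is rejected, falsely, in 4.0%.
- Only Autogenic works: MediMind–control is rejected, falsely, in 4.3%. MediMind–Autogenic is rejected in about 68%, correctly, because Autogenic Training is ahead.

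**5. The same pairs without the interaction gate**, Holm over the two contrasts, same summary and same 0.5 SD:
- Both work: MediMind–control is detected in 59%, against 46% through the gate (79% against 67% at 189).
- Only MediMind works: MediMind–Autogenic is detected in 82%, against 67% (95% against 87% at 189).

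**The case against.** Three stronger readings are tempting, and the article does not support them.

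**That the plan cannot test both hypotheses.** The sentence on Holm-Bonferroni comes directly after the one on orthogonal comparisons. In three groups those pairwise comparisons include both hypothesised pairs. What stands is that the step is conditional and the condition is not given.

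**That the trial would falsely claim success in 50% or 71% of cases.** Those figures describe one step. The plan is sequential, and nowhere says that a significant interaction alone establishes superiority. When both trainings work, the groups do differ and MediMind does beat control, so a significant interaction is a correct detection of something. Step 4 shows that the pairwise conclusions stay near 5% error. Group means at every time point will also be reported, so the direction would be visible.

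**That an optional Holm step leaves the familywise error uncontrolled.** With three groups, a significant overall test followed by one 5% test per pair is a closed procedure. Under no effect anywhere, any pair was rejected after a significant interaction in about 2.6% of runs. Repeating the pairs at several time points would need more care.

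It is also fair to say that an interaction followed by comparisons is conventional, and that a condensed article may leave the exact contrasts and the decisive time point to an analysis plan. I make no point of those omissions. The objection is to two things the article does state: a confirmatory criterion that does not address the hypotheses, and a follow-up whose named property excludes one of the two hypothesised pairs.

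**Conclusion.** The point holds in this limited form, and the text should be fixed. The confirmatory criterion is undirected. The orthogonal step can cover at most one of the two hypothesised pairs, and the only step that covers both is discretionary. The orthogonality result is algebra and rests on no assumed effect.

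The sizes do rest on assumptions, because the article gives no effect size or correlation. At 126 completers, with 0.5 SD and a correlation of 0.5, the interaction is significant in about 50% of trials when the trainings are equally effective (18% to 92% for effects of 0.3 to 0.8 SD). It is significant in about 71% when only Autogenic Training works. These are the frequencies of a result that a reader could mistake for support of the hypothesis. They are not false-claim rates of the whole plan; those stay near 5% if the pairwise tests are done and read.

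**What to change.** Delete the sentence on orthogonal comparisons and the condition on the Holm step. For each confirmatory outcome score, make two planned contrasts the decision rule: MediMind minus Autogenic Training, and MediMind minus control, on change from baseline and preferably adjusted for the baseline value. State the time point or average used. Apply Holm across the two contrasts in every case, and report each as a mean difference with a 95% confidence interval. Say that superiority over an arm is claimed only from the contrast with that arm, in the favourable direction. Keep the group by time interaction and partial eta-square as description.

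The cost is one paragraph, with the same data and software. The price is a first Holm threshold of 2.5%. On mean post-baseline change this lost no power in the scenarios in step 5, because the interaction gate goes as well. That gain depends on the summary chosen. At a correlation of 0.5, the raw change at a single wave has variance 2(1 − 0.5) = 1. The mean of three waves minus baseline has variance 2/3 + 1 − 2(0.5) = 2/3. The standard error for a single wave is therefore √1.5 = 1.22 times as large, and the advantage may disappear. This is a reason to adjust for baseline rather than analyse raw change.
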